### Metabolic and anthropomorphic outcomes

*Body composition* will be measured using dual-energy-x-ray absorptiometry (DXA) [48]. Specifically, fat mass, lean mass, body fat percentage, and bone mineral concentration will be quantified using whole-body dual-energy x-ray absorptiometry (DXA; Hologic QDR 4500; Hologic, Inc., Bedford, MA), which is a valid and reliable measure of body composition in healthy adolescents and adults, as well as cancer patients [48, 49].

### Biomarker outcomes

*Pro-inflammatory cytokines* interleukin 6 (IL-6), interleukin 1 beta (IL-1ß), and tumour necrosis factor alpha (TNF-α), anti-inflammatory cytokine interleukin 10 (IL-10), and C-reactive protein (CRP) will be measured in serum using MesoScale multiplexing [50], in consideration of the robust plate to plate reproducibility over time and the dynamic range with a lower limit of detection in the sub picograms per milliliter (i.e. pg/mL) range.

*BDNF* will be assayed from blood serum using MesoScale multiplexing [50], in consideration of the robust plate to plate reproducibility over time and the dynamic range with a lower limit of detection in the sub picograms per milliliter (i.e. pg/mL) range.

*Serotonin* will be measured using Serotonin ELISA (enzyme-linked immunosorbent assay) kits from Enzo Life Sciences [51] according to manufactures instructions. The ELISA is a plate-based assay technique designed for detecting and quantifying substances, including neurotransmitters and proteins.

*Lipopolysacchide* (LPS), a gram-negative bacterial endotoxin associated with intestinal permeability, systemic inflammation, and sickness behaviours, will be measured from serum using MesoScale multiplexing [50].

*Cortisol* will be analyzed using hair samples, which provide a reliable and valid measure of long-term cortisol activity [52, 53]. Hair cortisol will be quantified using liquid chromatography tandem mass spectrometry, and is reported to be more representative of total cortisol production relative to single saliva or serum measures, allowing us to quantify cortisol production over an extended period of time.

### Psychological and cognitive measurement

Post-Traumatic Stress symptoms will be measured using the Impact of Events Scale. Depression, anxiety, pain behaviour, fatigue, cognitive function, and social isolation will be measured via the NIH Patient-Reported Outcomes Measurement Information System (PROMIS). PROMIS is a set of person-centered measures that evaluates physical, mental, and social health, and is a valid measure of psychosocial outcomes among young adult cancer patients [54]. Details of these measures can be found in Table 1. An objective measure of executive function will also be collected using the Sustained Attention to Response Task (SART) is a computer-based go/no-go task that is designed to measure working memory, sustained attention, and impulse/inhibitory control [55], cognitive deficits that are frequently experienced by survivors who have received chemotherapy. The SART evaluates participants’ ability to withhold behavioral response to a single, infrequent target presented against a background of frequent non-targets [55]. Participants are asked to respond by pressing a button or the spacebar key after seeing the non-target on the screen and to inhibit their response to seeing the target. This task requires participants to be attentive to their responses, such that, at the appearance of a target, they can override the dominant motor response and substitute the directly antagonistic response (i.e. withhold button press). This study will use the online version of the SART, delivered through the Inquisit web software provider Millisecond.com. In this version of the task, a practice block (~ 30 s) is followed by two blocks (~ 3 min each), totaling approximately 6 min to complete the SART task.

**Table 1 Tab1:** Psychological and Cognitive Measures

Outcome	Measure	Scoring	Statement Example
Depression	PROMIS - Ca Item Bank v1.0 - Emotional Distress - Depression questionnaire: 30 items assessing presence and severity of depression	Patient rated on 5 point scale from “never” (1) to “always” (5)	“In the past 7 days… I felt helpless”
Anxiety	PROMIS - Ca Item Bank v1.0 - Emotional Distress - Anxiety questionnaire: 22 items re: symptoms of anxiety	Patient rated 5 point scale from “never” (1) to “always” (5)	“In the past 7 days… my worries overwhelmed me”
Post-Traumatic Stress Disorder (PTSD) symptoms	Impact of Life Events Scale: 22 items divided into 3 subscales that include avoidance, intrusion, and hyper-arousal. Evaluates symptom presence, severity, and degree of impairment	Patient rated 5 point scale from “not at all” (0) to “extremely” (4)	“How distressing has each difficulty been for you during the past 7 days with respect to cancer… I had trouble staying asleep”
Social Isolation	PROMIS Item Bank v2.0 - Social Isolation 14 item Short Form: evaluates feelings about perceived social isolation	Patient rated on a 5 point scale from “never” (1) to “always” (5)	“I feel isolated from others”
Pain Behaviour	PROMIS: Item Bank v.2.0 – Pain Behavior scale: 20 items evaluating behaviours related to pain	Patient rated from “Had no pain” (x), Never (1) to “Almost Always” (5)	“In the past 7 days, when I was in pain… I took medication for the pain”
Fatigue	PROMIS: Item Bank v1.0 - Fatigue - Short Form 8a scale: 8 items re: fatigue frequency and intensity	Patient rated on a 5 point scale from 1 (Not at all or Never) to 5 (Very much or Always)	“In the past 7 days… how run-down did you feel on average?”
Cognitive Function	PROMIS: Item Bank v2.0 – Cognitive Function: 32 items re: cognitive function including frequency and severity of cognitive concerns	Patient rated on a 5 point scale from “very often (several times a day)” (1) to “never” (5)	“In the past 7 days… I have had trouble concentrating”

### Procedure

Once identified, participants will be contacted by telephone or email to further verify inclusion and exclusion criteria, to obtain written informed consent, and schedule their first appointment. We will aim to assess participants at 3 different time points: < 2 months (T1), 3/4 (T2) and 5/6 (T3) months post chemotherapy, with healthy controls ideally being tested on the same day or within 5 days from when the patient is tested.

Participants will then receive a package via mail or in person, with instructions and materials for stool sample collection, and a link to fill out the self-report questionnaires, and demographic and clinical data online using REDCap. REDCap is a free, secure, browser-based application designed to support Electronic Data Capture for research studies provided through the Clinical Research Unit in the Cumming School of Medicine at the University of Calgary. Medical charts will also be accessed to confirm information regarding cancer diagnosis, treatment, glucocorticoid and antibiotic medication use, and mucositis.

Participants will be instructed to collect stool samples at home which can be stored in a freezer up to 3 days prior to their appointment, and to complete their online questionnaires prior to the appointment. On the day of their appointment, we will collect their stool sample from them. Participants will then be taken to have a hair sample collected for cortisol analysis (approximately 10 min), complete the cognitive task (i.e. the SART) on a computer (approximately 6 min), and complete their DXA scan (approximately 10 min), and have their blood drawn for serum biomarker analyses (approximately 10 min). This whole process should take approximately 45 min. Participants’ T2 and T3 month follow-up appointments will be scheduled at each subsequent visit and the procedure will be the same with respect to psychological and cognitive measures completed online, followed by their in person testing and biological sample collection. Participants will be provided a voucher for parking, and may choose from compensation in the form of either $30 at the end of the study or a pass to a fitness class after each appointment (they will have options to choose from in advance). If desired, participants will also receive a package with their individual results summarized and interpreted at the end of the study.

### Data analysis

*Objective 1* will examine whether chemotherapy is related to long-term gut dysbiosis as indicated by reduced alpha diversity in patients relative to controls, and from time points 1 through 3. Gut microbiota alpha diversity will be evaluated with the Shannon and Chao1 indexes using QIIME. To further examine differences in bacterial composition between the groups, LEfSe (linear discriminant analysis effect size) will be used to evaluate differential abundance between patients and controls, allowing us to identify the key bacteria that contribute most to the chemotherapy group having different bacteria relative to healthy controls. Linear Mixed Modelling (LMM) analyses will be used to examine differences across time and between groups. Group (survivors vs. healthy controls) and time (T1 – T3) will be fixed factors and individual subject will be a random factor.

*Objective 2* will first test group differences in gut microbiota, cytokines, LPS, 5-HT and BDNF, cortisol, and body composition using LMM as described above. We will test the interplay between the physiological systems of our model by examining associations between the gut microbiota, cytokines, LPS, 5-HT and BDNF, cortisol, and body composition using univariate correlations. Then multivariate regression models regressing cytokines, cortisol and body composition on gut microbiota diversity will be conducted, including variables that showed significant univariate correlations in the modelling. Covariates included theoretically based on the literature will include type of cancer diagnosis (i.e. blood or solid tumor), history of mucositis, glucocorticoid medication, antibiotic, and probiotic use, birth delivery mode, and breastfeeding in infancy.

*Objective 3* will first test group differences in cognitive and psychological parameters, gut microbiota diversity, and levels of 5-HT and BDNF using LMM as described above. We will test the relationships between gut microbiota, 5-HT and BDNF, and cognitive and psychological parameters using univariate correlations. Then multivariate regression models regressing psychological and cognitive parameters on gut microbiota diversity will be conducted, including variables that showed significant univariate correlations in the modelling. Covariates included theoretically based on the literature will as specified in objective 2.

*Objective 4* will explore relationships between clinical factors and all dependent variables, first using univariate correlations, followed by multivariate regression modelling to examine associations between cancer survivors’ clinical and demographic factors, and the dependent variables of gut microbiota alpha diversity and differential species composition, physiological parameters (i.e. cytokines, LPS, 5-HT, BDNF, and cortisol), body composition, and psychological and cognitive outcomes.

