### Cancer in young adults

The incidence of cancer among young adults has dramatically increased in recent decades [10], with over 8000 young Canadians diagnosed annually [12]. Between 1992 and 2013 the incidence of cancer has increased among young Canadian’s aged 15 to 29 by 18.2, and 11.9% among 30 to 39 year olds [12]. Considering their age at diagnosis, young adults experience unique personal, physical, and socioeconomic challenges throughout their cancer experience [12, 13]. As most young adult survivors are exposed to toxic therapies (e.g. chemotherapy) many will face years of chronicity living with treatment-related physical and psychosocial side-effects. For instance, Asher [14] reports that executive functioning, attention, concentration, processing speed, reaction time, motor speed and dexterity were the cognitive domains most frequently associated with chemotherapy induced cognitive impairment in all cancer populations. Additionally, Seitz et al. [15] examined the prevalence of posttraumatic stress, depression and anxiety among young adult survivors (*n* = 820) of adolescent cancer with a mean current age of 30.4 years [15]. They found that 90.5% cancer survivors had received chemotherapy, and 22.4% reported clinical symptoms of posttraumatic stress, anxiety and/or depression compared to only 14.0% of controls [15]. Posttraumatic stress symptoms in both male and female survivors were found to be more than three times that of controls [15]. Furthermore, female survivors reported symptoms of depression and anxiety significantly more often than controls, and 24.3% of the survivors met DSM-IV criteria for at least one mental disorder, relative to only 15.3% of the controls [15]. Indeed, the increased prevalence of young adult cancers in conjunction with the improved survival rates has resulted in a large group of survivors facing years of chronicity, unique challenges, and specific needs emerging from their cancer experience.

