### Present study

#### The objectives of the present study are to investigate

i.Whether chemotherapy is related to long-term attenuation of gut microbiota alpha diversity (i.e. gut dysbiosis, and which species differ significantly between patients and healthy controls);ii.Associations between gut microbiota, body composition (i.e. fat mass and lean mass, body fat percentage, and bone mineral concentration), inflammatory cytokine biomarkers (IL-6, IL-1B, TNF-a, IL-10), C-reactive protein (CRP), lipopolysaccharide (LPS), serotonin (5-HT), brain derived neurotrophic factor (BDNF), and cortisol;iii.Associations between gut microbiota, and psychological and cognitive outcomes including anxiety, depression, PTSD symptoms, pain, fatigue, and social and cognitive functioning;iv.Relationships between demographic and clinical factors, gut microbiota, and physiological, psychological and cognitive outcomes for survivors.

We hypothesize that:
i.Chemotherapy will be associated with significant reductions in gut microbiota alpha diversity at all time points, and relative to healthy controls;ii.Gut dysbiosis will be associated with increased risk for overweight/obesity, elevated pro-inflammatory cytokines, CRP and LPS, reduced serotonin and BDNF, and augmented levels of cortisol in survivors;iii.Gut dysbiosis will be associated with increased anxiety, depression, PTSD symptoms, pain, fatigue, and social and cognitive deficits in survivors;iv.There will be relationships between certain clinical factors (e.g. mucositis, antibiotic use), gut microbiota alpha diversity, and physiological, psychological and cognitive outcomes.

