##### Sample size and power

Target sample sizes of at least *n* = 50 cancer survivors and *n* = 50 healthy controls were selected based on sample sizes from previous studies on gut microbiota in cancer patients [17, 18] and practical considerations given the timeline and availability participants. With this sample size (*n* = 100 total), a medium effect size for group differences (Cohen’s d = 0.5, estimated with a power of 0.80, alpha = 0.05) can be detected using a one-sided test of the primary hypothesis that cancer survivors will have lower alpha diversity relative to controls [46].

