## Conclusion

Knowing what bacterial species are depleted after chemotherapy, how long these effects last, and the physiological mechanisms that may drive psychological and cognitive issues among survivors is a crucial step forward in gut microbiota and young adult cancer research. Understanding the bio-behavioural mechanisms that drive psychological and cognitive dysfunction among survivors will allow for tailored interventions to be developed. Future studies can aim to aid cancer patients and survivors by co-administering specific health promoting bacteria (i.e. probiotics), with the potential of preventing or reversing physical and mental health issues that many young survivors face.

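### Long-term dysbiosis is tied to a T1–T3 reduction with no pre-chemotherapy reference; define it as a survivor–control difference still present at T3, and word it as an association

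*Protocol article*

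**What the plan says.** The Data analysis section sets out Objective 1 as a test for "long-term gut dysbiosis as indicated by reduced alpha diversity in patients relative to controls, and from time points 1 through 3". Hypothesis (i), under Present study, is worded differently: "Chemotherapy will be associated with significant reductions in gut microbiota alpha diversity at all time points, and relative to healthy controls". The model for Objective 1 is a linear mixed model: "Group (survivors vs. healthy controls) and time (T1 – T3) will be fixed factors and individual subject will be a random factor". No interaction of group with time is named.

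The Procedure section plans "3 different time points: < 2 months (T1), 3/4 (T2) and 5/6 (T3) months post chemotherapy", so no sample precedes treatment. The inclusion criteria require every survivor to have had chemotherapy, and the control exclusion criteria rule out anyone with a history of cancer. Survivors of any stage may enter if they are stable and no longer on chemotherapy. Other past or current cancer treatment is not excluded, apart from allogeneic transplant.

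Sample size and power gives "Target sample sizes of at least *n* = 50 cancer survivors and *n* = 50 healthy controls", with a standardised difference of 0.5 "estimated with a power of 0.80, alpha = 0.05", one-sided. The primary hypothesis named there is between groups only: lower alpha diversity in survivors than in controls.

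The Conclusion (and the Abstract, in the same terms) speaks of "Knowing what bacterial species are depleted after chemotherapy, how long these effects last". The Discussion also describes the aim as finding effects of chemotherapy. Its limitations paragraph mentions neither the missing pre-treatment sample nor the absence of a cancer comparison group.

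**The concern.** Two things do not fit the design.

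**The time part of the criterion.** A reduction needs a reference from before the exposure. Here the earliest sample already follows chemotherapy. A deficit that lasts to six months gives a flat line from T1 to T3, and recovery gives a rise. Neither is a reduction over those visits. Hypothesis (i) can be read as reduced at each visit, while the Data analysis text can be read as falling from T1 to T3. The two readings give opposite verdicts on the same flat data.

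**What the group contrast can say.** It compares cancer plus all its treatment with no cancer. Surgery, radiotherapy, ongoing non-chemotherapy treatment and the disease itself go with chemotherapy. In addition, the group effect as described is an average over three visits, whereas the question is how long a difference lasts.

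At stake is the answer to the study's main question, whether the deficit persists, and the wording of a result on which probiotic interventions are meant to build.

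**Working it through.** **Inputs from the article:** 50 survivors and 50 controls, d = 0.5, one-sided alpha 0.05, three visits. **Assumed, because the article gives no figure:** unit SD, complete data, and a within-subject correlation ρ of 0.3, 0.5 or 0.7.

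**Step 1. The plan's own figure.** Power = Φ(d·√(n/2) − 1.645) = Φ(0.5 × 5 − 1.645) = Φ(0.855) = 0.804. The noncentral t with 98 degrees of freedom gives 0.799. The stated 0.80 reproduces. It applies to a comparison at one time point.

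**Step 2. Constant deficit of 0.5 SD at T1, T2 and T3.** The expected change from T1 to T3 in survivors is −0.5 − (−0.5) = 0, so a test for decline rejects at its alpha. For the group comparison on subject means, the variance is (1 + 2ρ)/3 and power = Φ(2.5/√((1 + 2ρ)/3) − 1.645):
- ρ = 0.3: Φ(3.42 − 1.645) = 96%
- ρ = 0.5: Φ(3.06 − 1.645) = 92%
- ρ = 0.7: Φ(2.80 − 1.645) = 87%

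**Step 3. Full linear recovery, gaps of 0.5, 0.25 and 0.** The expected change in survivors is a rise of 0.5 SD, the opposite direction to the literal criterion.

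**Step 4. Simulation of both patterns** (10,000 runs each; per cent significant for ρ = 0.3 / 0.5 / 0.7):

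| Test | Constant deficit | Full recovery by T3 |
|---|---|---|
| Group, averaged over visits (one-sided) | 96 / 92 / 87 | 53 / 44 / 40 |
| Decline T1 to T3 in survivors (one-sided) | 5 / 5 / 5 | 0 / 0 / 0 |
| Both required | 5 / 5 / 4.5 | 0 / 0 / 0 |
| Difference between groups in T1–T3 change (two-sided) | 5 / 5 / 5 | 55 / 70 / 89 |

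The averaged group test is significant in 40% to 53% of studies although the gap at T3 is zero. Averages can also coincide exactly: gaps of 1.0, 0.5, 0 and gaps of 0.5, 0.5, 0.5 both average 0.5, yet the first has closed and the second persists. The last row shows that a group-by-time comparison carries the information that separates the two.

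**Step 5. Attribution.** Suppose chemotherapy has no effect and a gap arises from the cancer, other treatment or selection. The one-sided test at a single visit is then significant with probability Φ(5 × gap − 1.645):
- 0.2 SD: Φ(−0.645) = 26%
- 0.3 SD: Φ(−0.145) = 44%
- 0.5 SD: Φ(0.855) = 80%

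These gaps are assumed. They show what the test cannot distinguish, not what is true of this cohort.

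**The case against.** A reader might infer that the study would miss a lasting deficit. The article does not support that. The powered primary hypothesis is the comparison with controls, the model has a group factor, and Step 2 shows good power for a flat deficit. Nowhere does the text say that both parts must be significant or that a flat slope counts as negative, so the 4.5% to 5% for both parts needs a rule that is not written. Read with hypothesis (i), the Objective 1 phrase may simply mean reduced throughout. What stands is that the two passages differ and that the phrase can be read either way.

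A reader might also infer that the objectives themselves claim causation. They do not: objective (i) and hypothesis (i) speak of a relation or an association, and the Discussion calls the study exploratory. The stronger wording is confined to the Abstract, Discussion and Conclusion.

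Nor are other treatments ignored. The article collects treatments received, confirms them from charts, and under Objective 4 relates survivors' clinical factors to diversity. That work is within survivors, however, and leaves the Objective 1 comparison with controls unchanged.

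Finally, an article condenses, and an interaction term may stand in a fuller plan. This is fair as to the term alone. It does not cure the stated criterion, which asks for a reduction over visits that have no pre-treatment reference.

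**Conclusion.** The concern holds in a limited form. The T1–T3 part of the dysbiosis criterion cannot show reduction by chemotherapy, and read as a decline it is uninformative for a lasting deficit and points the wrong way for recovery. The control comparison rescues detection of a gap but, as described, not the question of persistence, because it averages over visits. The sizes rest on a 0.5 SD effect, complete follow-up and assumed correlations of 0.3 to 0.7; the direction of the conclusion depends on none of these.

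On attribution, the design supports a statement about chemotherapy-treated survivors compared with cancer-free people. It does not support depletion by chemotherapy, and no subgroup analysis of these data can change that, since the cancer itself and the missing baseline remain. The study stays useful. Its definition of the endpoint and the wording of its conclusions should be corrected.

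**What to change.** 1. Reconcile hypothesis (i) with the Objective 1 text. Define long-term dysbiosis as a survivor–control difference in alpha diversity still present at T3.
2. Add a group-by-time term to the mixed model and report the survivor–control difference at T1, T2 and T3. Describe the T1–T3 change in survivors relative to controls as recovery or non-recovery.
3. Repeat the Objective 1 comparison, as a sensitivity analysis, without survivors who had abdominal or pelvic radiotherapy or who are on non-chemotherapy cancer treatment at the visit. The charts are already accessed for treatment data.
4. Whatever that analysis shows, word the Abstract, Discussion and Conclusion as a difference between chemotherapy-treated survivors and cancer-free controls. List the missing baseline and the missing cancer comparator as limitations.

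The cost is rewording, one model term, two chart variables and one repeat analysis, with no new visit or sample. The claim becomes narrower. A T3 contrast taken from that visit alone has about 80% power for 0.5 SD with complete data, against 87% to 96% for the average over visits. The sensitivity analysis has fewer survivors. If 20% to 50% were removed (assumed), 40 to 25 would remain against 50 controls, and single-visit power would be Φ(0.5/√(1/40 + 1/50) − 1.645) = Φ(0.712) = 76% down to Φ(0.5/√(1/25 + 1/50) − 1.645) = Φ(0.396) = 65%. It should therefore be read for consistency of the estimate, not for significance.

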### Demographics and clinical data

Clinical and demographic factors including current age, age at diagnosis, income, occupation, ethnicity, education, living arrangements, cancer diagnosis and treatments received, history of treatment related mucositis, current diet and exercise regimes, bowel habits, glucocorticoid medication, antibiotic, and probiotic use within the last 2 years, smoking, birth delivery mode (i.e. caesarian section vs. vaginal), and breastfeeding during infancy will be collected as these variables are known to impact the gut microbiota.

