## Discussion

Using the Microbiota-Gut-Brain Axis model and the biopsychosocial framework, this research aims to elucidate the long-term effects of chemotherapy on gut microbiota, and psychological, cognitive, metabolic, and immune outcomes in young adult cancer survivors. Moreover, this study will allow us to systematically explore and validate aspects the novel model proposed here; the Chemotherapy Driven Dysbiosis of the Microbiota-Gut-Brain Axis Model.

The design of this study is not without its limitations and we have taken steps to reduce potential confounds and bias. Although the sample size of this study is relatively small, it is comparable to other studies examining the effects of chemotherapy on gut microbiota, and taking into account feasibility, this sample size will produce adequate statistical power. Furthermore, while most studies typically require participants to have not taken antibiotics for at least 3 months prior to fecal collection, we have set the required time at 1 month. This is to account for the health status of the clinical population, tight timing between follow-up appointments, and to reduce potential attrition. Although colorectal cancers do frequently occur in young adults, we have chosen to exclude this specific diagnosis type from our sample as previous research suggests that specific changes in gut microbiota may be involved in the onset and/or progression of colorectal cancer [56, 57], and therefore present a potential confounding variable. Taking into consideration that the first data collection time point is very close to the final chemotherapy treatment, it is possible that hair sample collection may not be feasible for all patients, in which case hair samples may only be collected at time points 2 and 3 for some patients. However, this should still allow us to examine changes in cortisol over 3-4 and 5- 6 months post-chemotherapy since hair cortisol allows for retrospective cortisol quantification. Finally, as this novel study is exploratory in nature, we think that the methodological plan outlined will provide a rich and varied data set with which we will be able to answer our research questions. This knowledge will ultimately be used to inform future, larger studies and, most importantly, interventions.

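### Survivors may have had antibiotics 1–3 months before a stool sample and controls may not, and the Objective 1 group comparison does not account for the difference

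*Protocol article*

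**What the plan says.** **Eligibility.** The exclusion criteria set an antibiotic-free period before stool collection of 1 month for survivors and 3 months for controls. The Discussion acknowledges that 3 months is usual and says of its own rule: "we have set the required time at 1 month". The reasons given are the patients' health, the close spacing of visits and attrition. It does not mention that controls are held to the longer period, or what that does to the group comparison.

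**Data.** Demographics and clinical data lists "glucocorticoid medication, antibiotic, and probiotic use within the last 2 years" among items that "will be collected as these variables are known to impact the gut microbiota". Procedure adds: "Medical charts will also be accessed to confirm information regarding cancer diagnosis, treatment, glucocorticoid and antibiotic medication use, and mucositis".

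**Analysis.** For Objective 1, Data analysis states: "Group (survivors vs. healthy controls) and time (T1 – T3) will be fixed factors and individual subject will be a random factor". LEfSe then compares patients with controls. The covariate list for Objective 2, carried over to Objective 3, includes "history of mucositis, glucocorticoid medication, antibiotic, and probiotic use, birth delivery mode, and breastfeeding in infancy" and follows the description of the regression models. Objectives 2 and 3 reuse the Objective 1 mixed model for their group differences. Objective 4 relates clinical factors to alpha diversity among survivors.

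**Primary test.** Sample size and power fixes a one-sided test that survivors have lower alpha diversity than controls: 50 per group, alpha 0.05, power 0.80, Cohen's d 0.5.

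**The concern.** The two windows build an exposure difference into the comparison. A survivor sample may follow an antibiotic course that ended 6 weeks earlier; a control sample may not. The mixed model's group coefficient then carries chemotherapy and any remaining antibiotic effect together, and nothing in the stated model separates them. LEfSe has the same problem for individual taxa.

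If recent antibiotics lower diversity, the error runs the way the one-sided hypothesis points. A survivor deficit could be read as lasting chemotherapy-related dysbiosis when part of it comes from antibiotics. Taxa depleted by antibiotics could be reported as depleted by chemotherapy. The article's Conclusion proposes using such findings to choose bacteria for future interventions, so misattribution would carry forward.

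Unlike the confounding that any observational comparison has, this imbalance comes from the study's own eligibility rules, and the variable needed to examine it is already being collected.

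**Working it through.** **1. The plan's own figure.** Two-sample t-test, 50 versus 50, d = 0.5, one-sided alpha 0.05. Noncentrality = 0.5 / √(1/50 + 1/50) = 0.5 / 0.2 = 2.5 on 98 degrees of freedom. Power = 0.799, which reproduces the stated 0.80. The sample size is not in error for the test described.

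**2. When the 1–3 month window falls.** Visits are at under 2, 3–4 and 5–6 months after chemotherapy.
- T2: the window covers 0 to 3 months after chemotherapy (3 − 3 to 4 − 1).
- T3: it covers 2 to 5 months after (5 − 3 to 6 − 1).
- T1: even for a sample at 2 months, it starts 1 month before chemotherapy ended (2 − 3 = −1).

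The exposed share may therefore differ by visit, and at T1 exposure overlaps treatment.

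**3. Size of the bias.** Let p be the share of survivors exposed in the window and e the residual antibiotic effect in SD. Controls have p = 0 by design, so with no chemotherapy effect the expected group difference is p × e. The documents give neither p nor e; **both are assumed**. The rejection rate is the power of the one-sided test in step 1 with d replaced by p × e (nominal rate 5%).

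| p | e (SD) | Bias p × e (SD) | Rejection rate |
|---|---|---|---|
| 20% | 0.3 | 0.06 | 8.9% |
| 40% | 0.3 | 0.12 | 14.7% |
| 40% | 0.5 | 0.20 | 25.7% |
| 60% | 0.5 | 0.30 | 43.8% |
| 60% | 0.8 | 0.48 | 77.0% |

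This is a single-visit calculation. Repeated visits change the standard error, but not the bias at a given exposed share.

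**4. What adjustment does at one visit.** In 20,000 simulated studies with p = 0.3, e = 0.5 and no chemotherapy effect, the mean group estimate was −0.148 SD without an antibiotic term and 0.003 with it. Rejection was 17.3% and 5.0%. This assumes an additive effect.

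**5. What it costs in power.** Only unexposed survivors inform the restricted contrast, so SE = √(1/50 + 1/[50(1 − p)]). With p = 20%, 40%, 60%, the survivors left are 40, 30, 20. Power at d = 0.5 is 0.756, 0.692, 0.589, against 0.799.

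**6. A limit of adjustment over repeated visits.** The indicator occurs only in survivors and may be commonest at T1, so it can stand in for survivor recovery. Take assumed exposure of 60/30/10% at T1/T2/T3, within-subject correlation 0.5 and no antibiotic effect at all. With a deficit fading 0.6/0.4/0.2 SD, a model with group and time main effects falsely estimates the indicator at about −0.12 SD and shrinks the group coefficient by about 10%. With a deficit fading 0.8/0.4/0 SD, the figures are about −0.21 SD and 18%. Adding group-by-time brings the false estimate close to zero in a check with the same inputs, because exposed and unexposed survivors are then compared within a visit.

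**The case against.** **The covariates may simply be unstated.** The Abstract mentions covariates alongside regression and mixed models, and a condensed article can leave a full covariate list to another document. A reader might go further and infer that antibiotic use will never enter the primary model; the article does not say that. But it does set out the Objective 1 terms, and it attaches antibiotic use to the Objective 2 and 3 regressions. As written, the primary contrast does not account for it.

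**Antibiotics are examined elsewhere.** Hypothesis iv names antibiotic use in relation to alpha diversity, and Objective 4 studies clinical factors in survivors. Since controls are unexposed by design, any antibiotic effect in this window can be estimated only from survivors. That is right, but Objective 4 does not adjust the survivor–control difference.

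**The 1-month rule is disclosed and reasoned.** It is, and controls keep the period the article calls usual. The point here is the analysis that follows, not the choice of either window.

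**Antibiotics may be part of the treatment pathway.** Objective 1 asks whether chemotherapy is related to reduced diversity. If antibiotics given around treatment count as part of that relation, the unadjusted contrast answers a legitimate, broader question. This stands. It also defeats a rule that a deficit may be attributed to chemotherapy only if it survives adjustment: restriction may keep survivors with milder treatment or fewer complications and so push the contrast towards zero.

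**The adjusted model is not clean.** This also stands (step 6 of the working). Nor is a per-sample indicator equivalent to restriction once visits are repeated.

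**Conclusion.** The point holds in a limited form. The unequal windows, the collected antibiotic data and an Objective 1 comparison that does not use them are all on the page. If antibiotics lower alpha diversity, the survivor–control difference is biased towards the one-sided hypothesis.

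The size cannot be derived from the documents. The range of 0.06–0.48 SD rests wholly on assumed exposure of 20–60% and assumed effects of 0.3–0.8 SD. A reader might take the upper rejection rates as the study's expected false-positive rate. They are not: 77% needs both assumptions at their extreme, and one share applied at every visit. The direction, too, is conditional on antibiotics lowering diversity.

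The finding calls for supporting analyses and careful wording of the conclusion. It does not show the sample size to be wrong, and it does not call for replacing the primary contrast. That the study describes itself as exploratory limits the consequence but does not remove it, since the article sets a powered primary hypothesis.

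**What to change.** Keep the planned mixed-model contrast, and label it as the combined effect of chemotherapy and associated antibiotic use. Pre-specify beside it:

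- **(a) A restricted sensitivity analysis**, for alpha diversity and LEfSe, using only survivor samples with no antibiotics in the prior 3 months, the same period that applies to controls. This needs no additivity assumption.
- **(b) An adjusted mixed model**, adding a per-sample indicator of antibiotic use 1–3 months before that sample and a group-by-time term, so that the indicator does not stand in for survivor recovery.

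Obtain the date of the last antibiotic course for each visit through the questionnaire and chart review already planned. The article describes a 2-year history but does not say that courses are dated or that the history is updated at T2 and T3. Charts may also miss outside prescriptions.

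State the reading in advance: if the deficit shrinks materially in (a) or (b), report that chemotherapy and antibiotic effects cannot be separated, rather than attributing the deficit or the depleted taxa to chemotherapy alone.

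**Cost.** No new visits or samples: a dated antibiotic item at each visit, one restricted analysis and one extended model. The restricted contrast has single-visit power of about 0.76/0.69/0.59 at d = 0.5 with 20/40/60% exposed, so lost significance alone is not evidence of shrinkage; compare estimates and intervals. Because restriction may also select survivors with milder treatment, both analyses support the primary contrast and do not replace it.
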